### Control period

The control period will start immediately after the first assessment visit and will last 12 weeks (Fig. 1a). During the control period, participants will continue their usual activities and care.

### Intervention

Following the control period, a 20-week intervention period will start. It will consist of 4 vibration sessions a week performed on Galileo Basic vibration plates (Novotec Medical, Pforzheim, Germany). Participants will start from three 1-min bouts of vibration training at the frequency of 12 Hz with a gradual increase of both frequency and duration over the first 4 weeks to achieve the target frequency and time (3 sets of 3 min vibration training alternating with 3-min breaks between them). The target frequency of the vibration will vary depending on the intervention group (either 20 Hz or 25 Hz) and will be maintained for the remainder of the intervention period. Other parameters will be kept comparable in both treatment groups: amplitude – 2-4 mm, acceleration – maximum 11.4 g. Participants will stand barefoot on the plate with knees slightly bent, back straight, and arms free. For participants with poor balance, an adjustable metal frame will be used for safety purposes.

The vibration therapy frequencies (20 Hz vs 25 Hz) have been selected based on current literature and the Galileo vibration platforms manufacturing specifications. According to the latter, the main effect of low frequencies (12–20 Hz) lies in an improvement of muscle function and coordination whereas high frequencies (more than 20 Hz) have an impact on muscle power and muscle force [42]. According to the literature, 20 Hz is a typically recommended frequency for children with cerebral palsy [43]. In addition, 20 Hz has been shown to be the safest of low frequencies due to low vibration transmissibility to the head [19] and better coordination and posture stabilisation during the vibration training sessions [44]. 25 Hz was chosen as it is the highest frequency that has been used in long-term studies of side-alternating vibration training that involved children with cerebral palsy and that has demonstrated no severe adverse effects [24]. To summarize, the two frequencies were selected since they provide the optimal combination of expected results, as informed by extant literature and equipment specifications, and adherence to the ethical obligation of not compromising the patients’ safety.

Families have two options for where to perform the training: either at home or at a child’s school. In the case of home-based VT, parents/caregivers will have an instruction session at the Liggins Institute at the end of the second assessment visit on how to perform VT and provide supervision of home sessions. In order to monitor progress and provide feedback/support, a member of the research team will supervise home-based VT once every 2 weeks for the first 8 weeks and once a month for the remaining 12 weeks. In addition, parents/caregivers will be contacted by phone/ email for the follow-up. Vibration therapy at schools will be supervised by a member of the research team. Before the team member enters the school, an agreement form will be signed by the school’s principal/deputy principal to allow access. Parents of children who are performing vibration therapy at school sites will be followed up with in person (e.g. during assessment visits) as well as by phone and/or email.

Participants will be provided a VT diary with specifications of the frequency and duration of VT for each training session and will be asked to record the completed sessions, reasons for skipping sessions and comments regarding any adverse events.

### Primary outcome

The primary outcome measure is mobility, which will be assessed by the distance walked in the 6-min walk test (6MWT) at four-time points: baseline, in 12 weeks (the end of the control period), after 12 weeks of vibration therapy, and after completing 20 weeks of vibration therapy (Fig. 1b).

### Secondary outcomes

The secondary outcomes include body composition, muscle power, physical activity level, balance, gross motor function, respiratory function, and quality of life. All the outcomes will be assessed four times over the study period: baseline, at 12, 24, and 32 weeks (Fig. 1b).

### Other aims and outcomes

Participants’ fall history will be obtained using parents/caregivers recalls/reports of falls frequency and reasons during the study period by completing a falls diary.

### Clinical assessments/data collection

All participants will have four assessment visits at the Maurice and Agnes Paykel Clinical Research Unit (Liggins Institute, The University of Auckland) (Fig. 1b): 1 – baseline (T0), 2–12 weeks after the lead-in period (control) (T1), 3 – after 12 weeks of vibration therapy (T2), 4 – after completing 20 weeks of vibration therapy (T3). During the first visit, written informed consent will be obtained from a participant’s parent/guardian and, if possible, a child assent form from participants older than 7 years old. Information on demographic, ethnicity, medical history (including the history of birth, comorbidities, previous surgery, Botox injections, injuries, and admissions to the hospital) and medications currently taken will be recorded. We also will collect information on the frequency and duration of activities children undergo at school (e.g., physical education classes) and out of school (e.g., swimming, horse riding, walking with a dog, etc.). The procedures will be similar for all four visits and will also include anthropometric measurements, resting blood pressure and heart rate, mobility, body composition, muscle function, physical activity, gross motor function and respiratory function assessments, and the quality-of-life questionnaire.

### Anthropometric data

Height will be measured using a wall-fixed Harpenden Stadiometer (Holtain Ltd., Crymych, UK) three times, and the average of the three will be recorded to the nearest 0.1 cm. Weight will be measured on the calibrated electronic scale (Wedderburn WM206., NZ) without shoes and outerwear, when possible, to the nearest 0.1 kg. Based on the height and weight data, the Body mass index will be calculated electronically, using an online calculator available at https://www.heartfoundation.org.nz and recorded in kg/m^2^.

### Blood pressure, heart rate, and oxygen saturation

Blood pressure, heart rate, and oxygen saturation will be measured on the dominant arm in a sitting position after 10 min of rest prior to the start of functional tests. We will use a standard manual mercury sphygmomanometer with an appropriately-sized cuff to measure blood pressure and a finger sensor to record oxygen saturation and heart rate (Dinamap ProCare 100, GE Healthcare, Freiburg, Germany).

### Mobility

Two tests, a 6MWT and a 10-m walk test (10MWT), will be used to assess mobility. The 6MWT has been shown to be safe, easy to perform, reliable and valid in children with CP [45] and has been widely used in clinical trials in this population [16, 17, 46]. For the 6MWT, participants will be asked to walk as fast as they can between 2 cones separated by 25 m along a long, flat, straight indoor corridor for 6 min [47]. They will be able to stop and rest if required, and then continue walking until the 6 min are up. During the test, children will be closely supervised by an assessor and will be given standardized 6MWT instructions and encouragement [45, 48]. The total distance covered will be recorded to the nearest 0.5 m, along with the time taken to reach individual milestones (25 m). The participant’s perceived exhaustion will be assessed by using the OMNI-walk/run RPE scale before and after the test [49]. The test will be performed with shoes on; children may use their walking aid or orthotics, but not a wheelchair, to complete the test. For the 10MWT, a child will be instructed to walk as fast as (s) he can. The time to cover 6 m will be recorded, with two meters given for acceleration and two meters for deceleration. The test will be performed three times; the best time to the nearest hundredth of a second will be taken to calculate the walking speed (meters/sec). Verbal encouragement will be given during the walking task. The same assessor will be timing, with a stopwatch, all the participants to minimize the effect of human errors on the outcome. For both tests, if walking aids and orthotics are used, a note will be made in the record, and they will be consistently used for all 4 visits assessments.

### Muscle function status

Muscle function status will be measured by a number of assessments. Muscle strength will be measured with a hand-held dynamometer (MicroFET2, Hoggan Scientific, USA). Hand-held dynamometry has been reported as a reliable and valid measurement tool to assess muscle strength in clinical settings [50, 51]. Five muscle groups of the lower extremities (hip flexors and extensors, knee flexors and extensors, and ankle dorsiflexors) will be assessed using a “make”-technique [50]. The test will be performed by the same examiner, with the testing sequence kept in the same order at all the assessments. Standard instructions of “push as hard as you can” will be given to participants for each trial; consistent verbal encouragement will be given to children during timed, 3-s contraction period for all trials. Measurements will be performed three times for each muscle group with 30 s interval rest between assessments. The average of the three measurements will be taken for analysis.

The Leonardo™ Mechanography Ground Reaction Force Plate (Novotec Medical, Pforzheim, Germany) will be used to assess dynamic muscle function by chair rising test (CRT) and single two-leg jump test (S2LJT) [52]. The Force Plate has been reported as a reliable and valid instrument in children with CP [53]. The CRT test will be performed with a specially designed seat (Novotec Medical, Pforzheim, Germany) placed on the plate, with participants standing up and sitting down 5 times in a row as fast as possible with arms on chest. The test will be performed three times, with the best result recorded. For analysis, the total time to complete the test, maximum force and power in both legs will be used. For S2LJT, participants will be instructed to jump as high as possible using both legs and landing on the forefoot. The test will be performed three times after one practice, with the best result recorded. Variables of interest include the maximal jump height (m), the maximal total power per body weight (W/kg), maximal total force (kN), maximal velocity (m/s), and the Esslinger Fitness Index.

### Balance

The balance will be tested using the Leonardo™ Mechanography Ground Reaction Force Plate (Novotec Medical, Pforzheim, Germany) with the participant standing still with free arms for 10 s in three different positions: on both legs, on the right, and on the left leg (if a child can balance on one leg). The best result of the three trials will be recorded. The outcome parameter of the test is the standard ellipse area (cm^2^), which identifies postural stability [54].

### Gross motor function measure

Gross motor function measure (GMFM) is a clinical tool designed to evaluate changes in gross motor function in children with cerebral palsy both in clinical practice and for research purposes [55, 56]. It has demonstrated good test-retest reliability and responsiveness [57], and high construct validity [58, 59]. We will assess two dimensions from the original 88-item measure (GMFM-88): D (standing) and E (walking, running, jumping) [56]. The test will be performed in a playroom of the Clinical research unit at the Liggins Institute by the same research team member.

### Respiratory function

The respiratory function will be tested using a CareFusion MicroLab MK8 spirometer (Care Fusion; Chatham, Kent, UK). Before each measurement, the spirometer will be calibrated. Participants will be rested for 10 min before measurements. Before starting the test, subjects will be instructed on the test procedure, which will then be demonstrated by a researcher. A nose clip will be used during the test. Participants will perform a maximum forced inhalation (instructions: “Breath in as hard as you can”), followed by a powerful, quick, forced expiration (instructions: “Breath out as fast and as hard as you can”). At least three technically appropriate measurements will be performed, with the best result taken for statistical analysis. Measures will include forced vital capacity (FVC) (L), forced expiratory volume in 1 s (FEV1) (L), and ratio FEV1/FVC.

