### Body composition

Dual-energy X-ray absorptiometry (DXA) (Lunar Prodigy 2000, General Electric, Madison, WI, USA) will be used to determine body composition, including lean mass, percentage fat, bone mineral density (BMD) and bone mineral content (BMC). DXA is a safe, standardized instrument to measure bone density both in clinical settings and for research purposes [60]. A calibration check of the DXA machine will be performed on the day prior to starting measurements. We will perform two scans on each participant: total body and lumbar spine, that are recommended by the International Society for Clinical Densitometry, as the most accurate and reproducible sites in children to assess the BMD [60]. Total body, leg and trunk lean mass, and total fat mass will be derived from the total body DXA scan. The BMD and BMC of total body less head (TBLH) and lumbar spine (L1-L4) results will be presented and analyzed in real values (derived from the machine) and height-adjusted values (uses Lunar international reference database [61]). The necessity of presenting height-adjusted values in the pediatric population has been widely discussed and recognized as appropriate given the impact of short/ tall stature on the densitometry results.

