#### Data analyses

The data will be entered into an Excel workbook on password-protected computers, and later exported into SPSS v25 (IBM Corp, Armonk, NY, USA) and SAS v9.4 (SAS Institute, Cary, NC, USA) for statistical analyses. Baseline demographic and clinical characteristics of participants will be summarised by trial group allocation. Treatment evaluation of the primary outcome (i.e. mobility or distance covered during the 6-min walk test) will be performed on the principle of intention to treat, using data collected from all randomised participants. Data will be analysed using random effects mixed models with repeated measures, to account for the non-independence of measurements on the same participant. Models will incorporate as fixed effects the trial group allocation (20 vs 25 Hz), time-point (assessment II, III, or IV), and their interactions as fixed effects, as well as the participant’s GMFCS level; in addition, the baseline value of the outcome variable will be included as a covariate. There will be no imputation of missing data, as based on our previous studies, we expect very limited or no loss to follow-up. Nonetheless, for a small subset of secondary outcomes, such as certain functional tests on the Leonardo platform that cannot be performed by participants with GMFCS level III, only subgroup analyses will be carried out including solely participants with GMFCS level I-II. Model-adjusted differences between randomization groups and within groups (including the potential effects of treatment duration) will be calculated and reported with 95% confidence intervals. All statistical tests will be two-sided at *p* < 0.05, without adjustments for multiple comparisons.

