The main limitation of the study is the lack of a control group. We decided to utilize a study design where each participant acts as their own control for a number of reasons. Foremost, children with CP present a heterogeneous population with a variety of symptoms, which makes randomization with control and intervention groups problematic [66] and using each child as their own control adjusts for these issues. In this study, each participant serves as his/her own control, with the control period followed by an intervention period. This design has additional advantages. First, it eliminates the variability on the VT response due to participants’ individual characteristics because the statistical analysis is based on the within-subject comparison. Second, it is suitable for the CP population as their symptoms tend to be stable over time [1].

Another anticipated limitation of the study is that the number of the participants who have completed intended assessments may be uneven due to some subjects’ inability to perform some tests (e.g., S2LJT, chair rising test). However, we do not expect this to be a serious limitation, because, according to the eligibility criteria, children with a high level of disability will not be enrolled in the study.

In summary, the proposed study will expand the knowledge on the efficacy and effectiveness of side-alternating VT in children ages 5 to 12 years with mild to moderate CP. It will help understand the benefits and applicability of vibration therapy to improve the muscle and bone health, mobility, and other health aspects. As a result, the study will assist in defining more robust guidelines for the use of vibration therapy in young children with CP and will provide actionable insights to physiotherapists, families and the affected individuals into the optimal ways to use this therapeutic approach.

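### FVC and FEV1 are analysed in litres with no growth term, so their within-group changes and the 12- versus 20-week comparison include normal growth

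*Protocol article*

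**What the plan says.** All references are to the protocol article; no separate SAP is shown.

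- **Outcome form.** Under Respiratory function: "Measures will include forced vital capacity (FVC) (L), forced expiratory volume in 1 s (FEV1) (L), and ratio FEV1/FVC". The value analysed is the best raw manoeuvre: "At least three technically appropriate measurements will be performed, with the best result taken for statistical analysis". No z-score, percent-predicted or height-adjusted form is named.
- **Model.** Under Data analyses: "Models will incorporate as fixed effects the trial group allocation (20 vs 25 Hz), time-point (assessment II, III, or IV), and their interactions". GMFCS level is added, and "the baseline value of the outcome variable will be included as a covariate". Height, age and growth do not appear.
- **Contrasts.** The same section states: "Model-adjusted differences between randomization groups and within groups (including the potential effects of treatment duration) will be calculated". The Discussion concedes that there is no control group and says that "the statistical analysis is based on the within-subject comparison".
- **Size adjustment elsewhere.** Under Body composition, BMD and BMC are analysed both raw and height-adjusted, on the ground that "The necessity of presenting height-adjusted values in the pediatric population has been widely discussed and recognized as appropriate". Under Muscle function status, jump power is expressed per kilogram of body weight. Lean mass and dynamometer strength have no size adjustment.
- **Data available.** Under Clinical assessments/data collection, the procedures at all four visits "will also include anthropometric measurements, resting blood pressure and heart rate"; the Anthropometric data section includes height.

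**The concern.** Children aged 5–12 grow during a 32-week study, and lung volume rises with stature. In the stated model, GMFCS level and the T0 value are fixed for each child, so neither follows growth between assessments II, III and IV. Growth is absorbed by the time-point effect, and a within-group change from II to III or from II to IV carries 12 or 20 weeks of it.

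This matters for two stated aims. The Background hypothesises that vibration improves respiratory function and says the authors know of no earlier study of this in children with CP. The Discussion sets out to compare 12 with 20 weeks of therapy, and growth favours the longer period. With no untreated group, a vibration effect on FVC or FEV1 can be read only from changes over time, and all tests are at p<0.05 without multiplicity adjustment.

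**Working it through.** **Plan's own figure.** There is none to reproduce. The only stated sample-size calculation is for the 6-minute walk test (44 participants, 48 after drop-out); no effect size or SD is given for FVC or FEV1.

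**Inputs from the article.** Age 5–12 years; lead-in 12 weeks (T0 to T1); vibration for 20 weeks, assessed after 12 (T2) and 20 (T3); 44 participants before the drop-out allowance, 22 per group.

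**Assumed inputs (not in the article).** Growth 4–6 cm/year; height 115–145 cm; FVC 1.2–2.3 L, proportional to height to the power p with p = 2.0–3.0; SD of a between-visit change in FVC 0.10–0.20 L.

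**Step 1: growth-only change.** Proportional rise = (1 + rate × weeks/52 ÷ height)^p − 1.

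| Case | 12 weeks | 20 weeks |
|---|---|---|
| Lowest: 145 cm, 4 cm/year, p = 2.0 | (1 + 0.923/145)^2 − 1 = 1.3% | (1 + 1.538/145)^2 − 1 = 2.1% |
| Highest: 115 cm, 6 cm/year, p = 3.0 | (1 + 1.385/115)^3 − 1 = 3.7% | (1 + 2.308/115)^3 − 1 = 6.1% |

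Across the grid this is 19–67 mL at 12 weeks and 32–112 mL at 20. The T3 − T2 contrast carries the remaining 8 weeks, about 0.8 percentage points (2.1 − 1.3) to 2.4 (6.1 − 3.7).

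**Step 2: central case with zero vibration effect.** For 130 cm, 5.5 cm/year, FVC 1.7 L and p = 2.7, the formula gives 1.7 × 2.66% = 0.045 L at 12 weeks and 1.7 × 4.45% = 0.076 L at 20. A simulation that also varied height, growth rate and lung size between children (3,000 runs, n = 44, paired contrasts standing in for the mixed-model contrasts) gave:

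| Contrast | Mean (L) | Proportion p<0.05 for SD 0.10 / 0.15 / 0.20 L |
|---|---|---|
| T2 − T1, litres | +0.047 | 0.84 / 0.51 / 0.34 |
| T3 − T1, litres | +0.078 | 1.00 / 0.91 / 0.71 |
| T3 − T1, litres, one arm of 22 | +0.078 | 0.94 / 0.64 / 0.42 |
| (T2 − T1) − (T1 − T0) | about 0.00 | 0.05 / 0.05 / 0.05 |
| (T3 − T1) − (T1 − T0) | +0.032 | 0.23 / 0.13 / 0.08 |
| 20 vs 25 Hz at T3 | 0.00 | 0.05 / 0.05 / 0.05 |
| T3 − T1, height-scaled | 0.00 | 0.05 / 0.05 / 0.05 |

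The height-scaled row is a best case, because the exponent used for scaling was the one that generated the data.

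**Step 3: what the lead-in can do.** An equal-length comparison cancels growth at 12 weeks. At 20 weeks, 20 weeks of change are set against 12, leaving 8 weeks of growth (0.078 − 0.047 = 0.031 L, in line with the simulated 0.032 L).

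FEV1 has the same structure as FVC. In FEV1/FVC, numerator and denominator both grow, so the ratio largely escapes.

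**The case against.** The strongest reply is that the design has its own guard: each child is the control over a 12-week lead-in. Assessment II is modelled with T0 as covariate, so the lead-in change could be recovered and set against the treatment-period change. This stands in part. Such a contrast removes growth at 12 weeks, but the article does not specify it, and without scaling it does not cover 20 weeks.

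Second, the rejection rates for T2 − T1 and T3 − T1 apply only to those raw contrasts, which the article does not name as its test of benefit, and every input to them is assumed. This stands: they illustrate the mechanism and do not predict this trial's error rate.

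Third, a condensed article may leave derived forms of a secondary outcome to a SAP, the model description opens with the primary outcome, and the bone section keeps raw values alongside adjusted ones. This carries limited weight. The litre unit and the list of model terms are explicit, the same section goes on to discuss secondary outcomes, and the dual presentation is stated for BMD and BMC only. An analysis plan that follows this text would inherit the problem.

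A reader might infer that growth alone would produce a significant respiratory benefit, or that all respiratory results are compromised. The article supports neither. It gives no SDs, the randomised frequency comparison is unbiased, and FEV1/FVC is largely spared.

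**Conclusion.** The point holds for the non-randomised contrasts: within-group changes in FVC and FEV1 during vibration, and the comparison of 12 with 20 weeks. As specified, these contain normal growth and are biased upward. The direction follows from the stated units and model terms together with the age range. The size, about 1.3–3.7% over 12 weeks and 2.1–6.1% over 20, rests wholly on the assumed growth rates, heights and exponents.

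The wider claim that 20 weeks will look better than 12 is supported only as a shift in the mean of about 8 weeks' growth; the rejection rates for T3 − T1 do not carry over to T3 − T2. The same mechanism plausibly affects lean mass and dynamometer force, but that has not been quantified.

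These are secondary outcomes and the primary walk test is not at issue. The correction is still worth making before analysis, because it removes a bias from a stated hypothesis using data already collected.

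**What to change.** 1. For within-group and duration contrasts, analyse FVC and FEV1 as age-, sex- and height-standardised z-scores, naming the reference equations in advance. Keep litres as descriptive.
2. The alternative is log volume with log height at each visit as a time-varying covariate. In that case, model T0 as a response, not as a covariate. If the baseline volume stays in the model it already carries most of the between-child size information, so the height coefficient is pulled well below the true exponent and most of the growth remains in the time effect.
3. Prespecify the contrast of treatment-period change against lead-in change, scaled to equal time: (T2 − T1) − (T1 − T0) at 12 weeks and (T3 − T1) − (20/12)(T1 − T0) at 20.
4. Add visit height in the same way for lean mass and dynamometer force, as a supporting analysis.
5. State that the 20 versus 25 Hz comparison does not depend on these changes.

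**Cost.** No new data are needed, only a little more analysis work. The scaled 20-week contrast is noisy: with independent, equal-variance visit errors its variance is 1 + (32/12)² + (20/12)² = 10.9 units against 2 for T3 − T1, so its standard error is √(10.9/2) = 2.3 times as large. It therefore complements the size-standardised outcome and does not replace it.
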